### Sample size and analysis

Sample size was calculated for the primary outcome requiring the largest sample, i.e. time to work cessation. It was performed with PASS software [42] for time-to-event analyses. We assumed 5 years of follow-up and a rate of work cessation of 12.77% per year in the control group, based on the 40% work loss observed in controls over 4 years in Allaire’s RCT of VRC [34], and assuming an exponential distribution of time to work loss. A sample size of 420 subjects (210 per group) completing the study is necessary for 80% power, a 2-tailed Cox model-based score test, equivalent to the logrank test, at alpha = 0.05, to detect a 35% relative risk reduction (HR = 0.65) in the intervention vs. control group, which was considered a minimally clinically important difference (MCID), and is moderately conservative compared to the 42% risk reduction observed in Allaire’s study (HR = 0.58, 95% CI:0.34-0.99) [34]. Assuming 20% loss to follow-up, we will recruit a total of 526 subjects (263 per group). This sample will ensure adequate power for our other primary outcome, at-work productivity.

Appropriate descriptive statistics will be used to measure baseline characteristics of the two groups. Analysis of treatment effectiveness will rely on intention-to-treat (ITT) approach, so that all patients initially randomized will be included in the analysis, regardless of their compliance or drop-outs.

For the analysis of our first primary outcome, at-work productivity measured as a continuous variable will be tested for normality using the Shapiro-Wilk test [43]. If normality assumption is rejected, an appropriate transformation (e.g. such as logarithmic) will be employed to obtain an approximately normal distribution. Next, an Analysis of Variance (ANOVA) will evaluate the effect of the intervention on WIS measures at 2 years, adjusting for the 12 strata and blocking. We will also consider an Analysis of Covariance model after inspection of the baseline values in both treatment arms for factors such as WIS score, duration of disease, physician providing RA care, age, gender and risk factors for WD. If differences at baseline are observed, we will consider them as covariates. Since the power of these analyses will likely be less than the original ANOVA, post hoc power analyses will be conducted if these appear to be clinically meaningful adjustments.

In the analysis of our second primary outcome, time-to-event (survival) methodology will compare the risk of work cessation in the intervention and control groups. Subjects employed until end of their follow-up (study end, death or time of loss to follow-up, whichever occurs earlier) will be censored. First, Kaplan Meier ‘survival curves’ and logrank test will estimate and compare the proportions of subjects who continue being employed in the intervention and control groups. Next, multivariable Cox Proportional Hazards (PH) regression model [44] will be employed to estimate the adjusted Hazard Ratio (HR) with 95% CI, associated with the intervention after controlling for potential risk factors for WD that may be imbalanced at baseline, despite randomization, and for other important predictors, such as age, gender, RA duration at baseline, and physician providing RA care, whose omission could induce bias toward the null in time-to-event analyses [45]. We will use a flexible extension of the Cox model [46], which will allow us to estimate how the HR reduction due to intervention changes over time, if the proportional hazard assumption (that the intervention effect remains constant over time) is rejected.

For analyses of secondary outcomes, time-to-event methods will be employed for dichotomous outcome variables (e.g. time to temporary work cessation), and comparison of means between intervention and control groups will be employed for continuous variables (e.g. measures of absenteeism, job satisfaction, self-efficacy and risk factors for WD), as described above for the primary outcomes.

For the second primary outcome (time to work cessation), an interim analysis will be performed at 2 years of follow-up. We will use the same method as for the primary analysis and will employ the PETO criteria to adjust the overall type I error for multiple testing [47]. Specifically, we will use a conservative type I error of 0.001 for the interim analysis, which will allow us to maximize the power of the final analyses of the 5 year outcomes, which will employ the conventional 0.05 significance level.

We will also examine the incremental costs and benefits of receiving the intervention versus standard of care. Both a cost-effectiveness analysis and a cost-utility analysis will be performed. The outcome of our analysis will be the incremental cost-effectiveness ratio (ICER), which is the difference between the mean costs of providing competing interventions divided by the difference in effectiveness. Based on the primary outcome of the RCT, we will determine the incremental cost of the intervention per work cessation avoided relative to standard treatment. Because cost-effectiveness analyses are not robust to quantity or quality of life, we will also conduct a cost-utility analysis, where the primary outcome is the quality adjusted life year (QALY). Using health utilities measured by the EQ-5D and SF-6D, we will conduct a cost-utility analysis in which the incremental cost of the intervention relative to standard therapy per QALY gained will be determined. Important aspects of economic evaluations conducted alongside an RCT are excluding protocol driven costs, and dealing with missing data due to attrition. We will follow recommendations by the International Society for Pharmacoeconomics and Outcomes Research for missing cost and effectiveness data. We will use a combination of imputation and bootstrapping to quantify uncertainty due to missing values and finite study sample size. We will use propensity scores, stratified by treatment group, for imputing missing costs and effectiveness data due to attrition.

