### Outcome measures

#### **
*Primary work outcomes*
**

The first primary outcome will be presenteeism, or at-work productivity, measured over 2 years, using the Work Instability Scale (WIS-RA) [36]. Developed for RA, the WIS measures mismatch between functional ability and work demands, and was designed to identify individuals at high risk of work loss warranting referral for vocational assessment. It has been shown to have good psychometric properties, including construct validity [37], and be effective at predicting future work transitions [38]. However, a drawback of the WIS is that it does not permit the calculation of associated costs. Therefore, for the purpose of the cost-utility analysis, at-work productivity will be measured using the Work Productivity and Activity Impairment – Specific Health Problem (WPAI-SHP) scale [39]. The WPAI-SHP measures overall impairment in activities (from work time missed, impairment while working, and activity impairment outside of work) due to a health problem, expressed as percent impairment, which can be used to calculate associated cost. Statistically significant improvement in both the WIS and the WPAI-SHP were observed in our pilot study.

The second primary outcome will be time to work cessation, measured over 5 years of follow up. Work cessation is defined as complete cessation of work for more than 6 months, the standard duration used by insurance companies to define permanent WD, and also consistent with definitions of WD in the employment literature [40]. This definition will capture WD from all health reasons (i.e. not only related to arthritis), including early retirement, work cessation for personal reasons, and prolonged unemployment periods when people are looking for another job, but will not capture temporary WD, sick leave, or short periods of unemployment of less than 6 months duration. Whether or not work cessation should be restricted to arthritis related work cessation is an issue of debate in the arthritis employment literature. Because of difficulties attributing work cessation to a single cause (i.e. the decision is often multifactorial and arthritis may have played some role in the decision), it is generally recommended that all-cause work cessation be measured in studies including a control group [41].

#### **
*Secondary work outcomes*
**

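### A Shapiro-Wilk test on the outcome decides whether the first primary comparison (WIS at 2 years) is made on the original scale or on an unnamed transformed scale, so its effect measure is not fixed in advance

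*Protocol article*

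**What the plan says.** The protocol article, under Outcome measures, makes at-work productivity on the Work Instability Scale (WIS) the first primary outcome, measured over 2 years. Under Sample size and analysis, this outcome, as a continuous variable, is to be "tested for normality using the Shapiro-Wilk test". The consequence of rejection follows: "If normality assumption is rejected, an appropriate transformation (e.g. such as logarithmic) will be employed to obtain an approximately normal distribution". The comparison comes after that step, in a sentence that closes with the randomization blocks as a further adjustment: "Next, an Analysis of Variance (ANOVA) will evaluate the effect of the intervention on WIS measures at 2 years, adjusting for the 12 strata and".

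The rejection level of the test is not given, and the transformation is not named beyond the example. Nothing in the article keeps the difference in mean WIS as the primary result whatever the test shows, or says how a transformed effect would be reported. Continuous secondary outcomes are to be analysed by comparison of means, in a sentence that ends "as described above for the primary outcomes".

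**The concern.** The pre-test is the gate to the primary analysis. Three features make it a poor gate.

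- It looks at the outcome variable, whereas the normality assumption of an ANOVA concerns the residuals.
- Its power to reject grows with sample size, while the need for normality in a comparison of means shrinks. At several hundred values it reacts to departures that do no harm.
- Rejection leads to a choice that is not specified. A difference in mean WIS points is a different quantity from, say, a ratio of geometric means, and the reader cannot know beforehand which one the trial will report.

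At stake are the effect measure and clinical interpretation of a primary outcome, settled after the 2-year data are seen. This is a rule the protocol states, so a later analysis plan would have to override it and not merely fill a gap.

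**Working it through.** **1. How many values the test would see.** The only sample size calculated is for time to work cessation: "A sample size of 420 subjects (210 per group) completing the study is necessary for 80% power". It reproduces.

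- Hazard = -ln(0.60)/4 = 0.1277 per year.
- Five-year event probabilities: 1 - exp(-5 × 0.1277) = 0.472 in controls, and 1 - exp(-5 × 0.1277 × 0.65) = 0.340 with HR 0.65. The mean is 0.406.
- The Schoenfeld formula gives 170 events for 80% power at two-sided 0.05, so N = 170/0.4058 = 419 (stated: 420).
- Loss to follow-up: 210/0.8 = 262.5, so 263 per group and 526 in total, as stated.

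I take 420 as the working number of WIS values. The number available at 2 years could be higher or lower, so 340 and 526 are shown where they were run.

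**2. How often the test rejects.** The article gives no range, mean, SD or skewness for WIS and no rejection level. The shapes and the 0.05 level below are therefore assumptions (1,000 to 1,500 simulated samples per case).

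| Assumed shape | n = 340 | n = 420 | n = 526 |
|---|---|---|---|
| Exactly normal | – | 4% to 6% | 5% |
| Normal, rounded to whole points, SD 5 | 33% | 46% (49% in repeat runs) | – |
| Skewness 0.3 | – | 60% | 70% |
| Skewness 0.5 | 92% | 97% | 99% |
| Integer score bounded at 0 and 20, mean 10, SD 5 (skewness 0) | 100% | 100% | 100% |

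**3. Whether the rejected shapes harm the raw comparison.** With 210 per arm and no treatment effect, the two-group t comparison rejected in 5.4% of 8,000 trials for the bounded 0–20 score and in 4.8% for the outcome with skewness 0.5. The nominal rate is 5%, so the departures that trigger the rule leave the raw-scale test intact.

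**4. What a change of scale does.** The difference detectable with 80% power at 210 per arm is (1.960 + 0.842) × √(2/210) = 0.273 SD. With SD 5 this is 0.273 × 5 = 1.37 points. For the bounded 0–20 score with that shift (3,000 trials):

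- power was 79.9% on the raw scale and 74.4% with log(x+1), a loss of 5.5 points;
- the two analyses disagreed on significance in 11% of trials;
- log(x+1) moved skewness from 0 to about -1.7, and normality was still rejected in every sample.

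Across other assumed bounded shapes, the change in power with log(x+1) ran from -5.5 to +1 points.

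**5. Type I error of the rule itself.** Applied mechanically (Shapiro-Wilk on the pooled outcome, log(x+1) if rejected, 210 per arm, four assumed bounded shapes, 4,000 trials each), the rule gave 4.4% to 5.7%, against 4.6% to 5.7% for the raw test. Taking the smallest p-value among raw, log and square root gave 6.4% (3,000 trials; standard error √(0.064 × 0.936/3000) = 0.45 points).

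**The case against.** The strongest reply is that the rule, followed as written, does little damage to error rates. Its criterion is approximate normality, not significance, and the mechanical version held type I error at about 5%. That stands. A reader might infer that the pre-test inflates the false-positive rate. The text does not support this, because the 6.4% figure arises only if an analyst picks the best of three scales, which the plan does not provide for.

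Second, the logarithm is only an example. It is tempting to object that a log is undefined at a score of zero or can worsen left skew. Those objections hit the example, not a fixed rule: a transformation that failed in this way would also fail the protocol's own aim of an approximately normal distribution. This stands too, and what remains is that no transformation is named.

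Third, a reader might infer that the same step governs the continuous secondary outcomes, such as days missed. The closing phrase of that sentence could carry the step over, but the sentence also covers time-to-event methods and otherwise specifies only a comparison of means. Carry-over is possible, not stated.

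Fourth, testing the outcome instead of residuals may matter little in practice. With a treatment effect near 0.27 SD the two have nearly the same shape, unless stratum effects are large, for which the article gives no data.

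None of this answers the main point: the scale of a primary result is left to a data-dependent step that the comparison of means does not need.

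**Conclusion.** The concern holds in a limited form. The protocol lets a normality test on WIS decide the scale of the first primary comparison, with the transformed scale unnamed and chosen after the 2-year data are seen. At about 420 values the test would often reject for departures that do not disturb a comparison of means: from about 46% for rounded normal data to about 100% for bounded integer scores. It would be too strong to call rejection near certain, since these rates rest on assumed shapes and an assumed 0.05 level, and the rounded-normal case rejects in fewer than half of samples.

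The cost is an effect measure and clinical meaning that are not fixed in advance, with a possible power loss of about 5 to 6 points in the least favourable log case examined. Validity in the sense of type I error is not in question. This should be changed, but it does not undermine the trial.

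**What to change.** Delete the Shapiro-Wilk step and the conditional transformation. State that the primary analysis of the first primary outcome is the adjusted difference in mean WIS at 2 years on the original scale, with its confidence interval. Robust standard errors or a bootstrap interval are acceptable if there is worry about the error distribution. Keep any transformed or rank-based analysis as a sensitivity analysis, named in advance.

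Say whether the reference back to the primary outcomes is meant to bring the normality step to the continuous secondary outcomes. If it is, make the same change there.

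This is a free improvement: it changes wording only and needs no further participants or data.

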## Methods/design

### Study design

Our study design is consistent with CONSORT recommendations for RCTs, 2010 update [32] and extension for trials of non-pharmacological treatments [33]. Participants will be stratified by location and arthritis type and randomized 1:1 to receive either our program, or “usual care” as initiated by their physician and supplemented by printed material about work and arthritis. Participants will be followed for 5 years, the estimated time required, according to our power calculations, to observe a difference in work cessation similar to that in Allaire’s RCT [34]. After 2 years, analysis of our first primary outcome, at-work productivity, will be performed, along with an interim analysis of the second primary outcome, work cessation. If a significant difference in work cessation is observed between the two groups, the RCT will be terminated prematurely. Because of the nature of the intervention, participants cannot be blinded. Ethics approval was obtained from the University of British Columbia Research Ethics Board (H11-03527).

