### Data collection

Data will be collected on demographics, disease variables, co-morbidities, quality of life, costs, work-related risk factors for WD, and work outcomes, using a self-administered online questionnaire. Work outcomes, costs and quality of life will be assessed every 6 months, and other data once yearly. To evaluate co-interventions received in both groups, data will also be collected every 6 months about IA treatment received, “usual care” received from physicians and allied health professionals, information sought about employment issues, use of services specifically targeted at employment, and job accommodations made.

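### The primary test of at-work productivity uses only the 2-year WIS score, leaving the 6-, 12- and 18-month scores and early drop-outs out of it; one mixed model with one pre-named contrast would align outcome and test

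*Protocol article*

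**What the plan says.** Three sections of the Protocol article bear on the first primary outcome.

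- Outcome measures: "The first primary outcome will be presenteeism, or at-work productivity, measured over 2 years, using the Work Instability Scale (WIS-RA"). No average, slope or single visit is named there.
- Data collection: "Work outcomes, costs and quality of life will be assessed every 6 months, and other data once yearly". The WIS is listed among the primary work outcomes, so four follow-up scores fall due by month 24 (6, 12, 18 and 24 months).
- Sample size and analysis: "an Analysis of Variance (ANOVA) will evaluate the effect of the intervention on WIS measures at 2 years", with adjustment for the randomization strata and blocks. Baseline WIS is only a possible covariate: "We will also consider an Analysis of Covariance model after inspection of the baseline values in both treatment arms for factors such as WIS score".

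Study design adds the timing: "After 2 years, analysis of our first primary outcome, at-work productivity, will be performed". That fits a test at month 24 or a test of the whole period. On the analysis set, Sample size and analysis says that "all patients initially randomized will be included in the analysis, regardless of their compliance or drop-outs", and the same section assumes 20% loss to follow-up over the study.

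**The concern.** The outcome is worded as a 2-year period and collected at four visits, but the stated test uses one visit. Two things follow.

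First, the definition and the analysis do not clearly name the same quantity. The program is time-limited: five biweekly sessions, then two consultations, each with a follow-up a month later. An effect present at 6 to 18 months that had faded by month 24 would give a null primary result, while one that built up slowly would give a positive one. Which of these counts as success should be settled in advance.

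Second, an ANOVA on the 24-month score has nothing to work with for a participant lost before month 24, unless that score is imputed. This sits poorly with the promise to analyse everyone randomized, when earlier scores from many of those lost will already have been collected.

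**Working it through.** **The plan's own figure.** The only sample size given is for time to work cessation, and it reproduces. Control hazard = −ln(0.60)/4 = 0.1277 per year. Five-year event probabilities are 0.472 (control) and 0.340 (HR 0.65), mean 0.406. Schoenfeld's formula needs 170 events, and 170/0.406 = 419, against 420 stated. With 20% loss, 210/0.80 = 262.5, so 263 per group and 526 in all. The sample size is not in question. For WIS the article gives no difference, standard deviation or within-person correlation, so what follows is in standard-deviation (SD) units and over a range of correlations.

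**Averaged contrast against the single score.** Assume equal variances and one common correlation r between visits (compound symmetry). The variance of a mean of four scores, relative to one score, is (1 + 3r)/4. The detectable difference at 24 months with 210 per arm, 80% power and two-sided 0.05 (the level stated for work cessation, assumed here for WIS) is (1.960 + 0.842) × √(2/210) = 0.273 SD. For the average, multiply by √[(1 + 3r)/4].

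| r (assumed) | variance ratio | SE smaller by | detectable difference | power at a constant 0.273 SD |
|---|---|---|---|---|
| 0.5 | 0.625 | 21% | 0.216 SD | 94% |
| 0.6 | 0.700 | 16% | 0.229 SD | 92% |
| 0.7 | 0.775 | 12% | 0.241 SD | 89% |
| 0.8 | 0.850 | 8% | 0.252 SD | 86% |

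The last column assumes the same effect at all four visits. In general the average has more power only if (average effect)/(24-month effect) exceeds √[(1 + 3r)/4], which is 0.84 at r = 0.6 and 0.88 at r = 0.7. An effect growing in equal steps to month 24 has an average of (0.25 + 0.50 + 0.75 + 1)/4 = 0.625 of its final value. Averaging would then lose power at every r in the table.

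With baseline WIS in both models, the variance ratio is [(1 + 3r)/4 − r²]/(1 − r²): 0.531 at r = 0.6 and 0.559 at r = 0.7, so the standard error is 27% and 25% smaller. This compares two baseline-adjusted analyses, whereas the ANOVA as stated does not include baseline WIS.

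**24-month contrast.** With complete data, the earlier visits add essentially nothing to the 24-month difference beyond what baseline adjustment gives, and a single-visit ANCOVA has that too. The gain comes from drop-outs. The article does not give loss by month 24. If the 20% accrues at a constant rate over 5 years, it is 1 − 0.80^(2/5) = 8.5%, or about 45 of 526. If all of it falls before month 24, it is 20%, or about 105. Full recovery of these scores would shrink the standard error by at most 1 − √(1 − 0.085) = 4% and 1 − √(1 − 0.20) = 11% respectively. Real recovery would be less.

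**What the model does not settle.** At the design's own rates, work cessation by 2 years is 1 − exp(−2 × 0.1277) = 22.5% in controls and 1 − exp(−2 × 0.1277 × 0.65) = 15.3% in the intervention group. If WIS can be scored only while working (an assumption), these participants have no 24-month score, and unequally so by arm. This affects the ANOVA and the mixed model alike.

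**The case against.** The strongest reply is that nothing is mismatched. The article uses the same phrasing for work cessation over 5 years, where it describes the length of follow-up. Read that way, definition, timing and test all point to a 2-year endpoint. That endpoint is also sensible: the Background section reports favourable proof-of-concept results at 12 months, so a test at 24 months asks whether benefit lasts. This reply largely stands. What remains is that work cessation is analysed with all its event times across the period, while WIS is analysed at one visit, so the shared phrase does not settle which summary is meant.

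A reader might go further and infer that the trial fails to answer its own outcome, throws away three of four scores, or cannot tell a lasting effect from a fading one. The documents do not support this. No average is defined anywhere. A condensed article does not show that earlier scores go unused outside the primary test, and a 24-month test addresses a lasting effect directly.

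It is also true that making the average primary changes the target of estimation, and that its precision gain depends on assumed correlations and on the shape of the effect. The consultations come after the group sessions and leave recommendations to be implemented, so an effect that builds is as plausible as one that fades.

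The drop-out argument is not met by any of this. The article describes imputation only for the economic evaluation. Handling of missing WIS scores may be in the full plan, but the stated single-visit ANOVA does not itself use partial data.

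**Conclusion.** The point holds as a modest, inexpensive improvement. The stated primary test gives no role to the 6-, 12- and 18-month WIS scores, the sections leave room for two summary measures, and participants lost before month 24 drop out of the test unless imputed, despite the promise to include everyone randomized.

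The size depends on the contrast chosen. For the 2-year average, the standard error is 12% to 16% smaller at r = 0.6 to 0.7 (21% at 0.5, 8% at 0.8). More power follows only if the average effect is at least about 84% to 88% of the 24-month effect at r = 0.6 to 0.7. For the 24-month contrast, the gain from the extra visits is limited to information recovered from drop-outs. Compound symmetry and the values of r are assumptions.

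It would be wrong to conclude that the 24-month target is invalid or that the WIS comparison lacks power; nothing in the article shows either.

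**What to change.** Replace the ANOVA with one repeated-measures mixed model on the 6-, 12-, 18- and 24-month WIS scores, with terms for arm, visit, arm-by-visit, randomization strata and baseline WIS. Fix baseline WIS as a covariate in advance, without first inspecting it for imbalance.

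Name one primary contrast before any data are compared by arm, and word Outcome measures and Sample size and analysis to match it. Either keep the 24-month difference, as now tested, and define the outcome as WIS at 24 months, or keep the period wording and test the difference averaged over the 2 years. Report the other contrast as supportive, so that readers can see whether an effect lasts, fades or builds.

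The cost is plan wording and slightly more modelling; the scores are already scheduled. The model relies on data being missing at random, and participants with no follow-up score still contribute nothing when baseline is a covariate. If WIS is scored only while working, the plan also needs a separate statement on how scores after work cessation are treated, because the mixed model does not by itself resolve that.

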## Background

Work disability (WD) is a common and early outcome of inflammatory arthritis (IA), with a major impact on quality of life and a high cost to those affected, their families and society [1,2]. Arthritis and musculoskeletal conditions are the leading cause of long-term WD in many countries, including Canada and the US [3,4]. Recent studies have also drawn attention to the importance of decreased productivity while at work, or presenteeism [5]. Despite the importance of the problem, there has been little research on interventions to reduce the impact of arthritis on employment [6-9]. Lack of employment services has also been identified by people living with arthritis as an important unmet need in qualitative studies [10-12]. It represents an important gap from a clinical care and a health services research perspective.

To close this care gap, we have developed and pilot tested a novel intervention targeting employed people with IA, to prevent WD and improve at-work productivity [13]. Our “Employment and Arthritis: Making It Work Program” is unique in that it combines the benefits of group sessions and self-learning modules aimed at enhancing self-management of work-related problems, and individualized assessments by employment-related health professionals, including an ergonomic assessment by an occupational therapist (OT) and job retention vocational rehabilitation counselling (VRC). Program development was based on a strong theoretical background, the self-management approach proven effective in arthritis management [14,15] and the precede-proceed model [16-18], a validated model successfully used for developing health education programs. Program content was selected to modify known risk factors for WD and problems at work identified in initial focus groups [10]. A proof of concept study of the intervention showed favourable results after 12 months of follow up [13]. The program has now been converted to a web-based format to allow broader dissemination of the program, and to address feedback from participants who found it difficult to attend sessions at the end of a work day, given the fatigue and difficulty commuting associated with their IA. This evolution is consistent with recent trends in adult learning, health education and in self-management programs [19-31].

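### The 2-year WIS analysis conflicts with the promise to include all randomized patients, because no rule covers participants who have stopped work

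*Protocol article*

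**What the plan says.** Under Sample size and analysis, the protocol article adopts intention to treat (ITT) for treatment effectiveness and explains it to mean that "all patients initially randomized will be included in the analysis, regardless of their compliance or drop-outs". The next paragraph sets the first primary analysis: "an Analysis of Variance (ANOVA) will evaluate the effect of the intervention on WIS measures at 2 years, adjusting for the 12 strata and blocking". Analysis of covariance, with baseline WIS among the candidate covariates, is considered only if baseline differences are seen.

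Outcome measures defines the variable: "The first primary outcome will be presenteeism, or at-work productivity, measured over 2 years, using the Work Instability Scale (WIS-RA"). The same section says that "the WIS measures mismatch between functional ability and work demands, and was designed to identify individuals at high risk of work loss" and reports that the scale predicts later work transitions. The Background describes presenteeism as lost productivity in people who are at work.

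The second primary outcome is time to work cessation: "Work cessation is defined as complete cessation of work for more than 6 months". It counts cessation for any reason.

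Data collection adds that "Work outcomes, costs and quality of life will be assessed every 6 months, and other data once yearly".

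**The concern.** A scale that sets ability against work demands has no current value in someone who has no work. The article fixes the population (everyone randomized), the variable (an at-work scale), the time (2 years) and the method (ANOVA). It gives no score, rank or other rule for a participant who has stopped, so these four choices do not fit together.

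This differs from ordinary missing data. The event that removes the score is the trial's other primary outcome, and the program is intended to prevent it. By the article's own account, the people most likely to leave work are those with poor WIS scores. If the program keeps such people employed, they stay in the intervention mean while their counterparts drop out of the control mean. The groups compared are then no longer the groups randomized, and a real improvement in WIS would be understated.

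**Working it through.** **Inputs from the protocol article (Sample size and analysis).** Control work loss 40% over 4 years, exponential times, hazard ratio 0.65, two-sided alpha 0.05, 80% power, 5 years of follow-up, 420 completers, 20% loss to follow-up, 526 recruited (263 per group).

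**Step 1: reproduce the plan's figures.**
- Control hazard = -ln(0.6)/4 = 0.1277 per year, as stated.
- Events needed (Schoenfeld) = 170.
- Five-year event probabilities: 1 - exp(-0.1277 × 5) = 0.472 for control, and 1 - exp(-0.1277 × 0.65 × 5) = 0.340 for intervention. The mean is 0.406.
- N = 170/0.406 = 419, against the stated 420.
- 210/0.8 = 262.5, rounded up to 263 per group, or 526.

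The design figures reproduce, so the same rates can be read at 2 years.

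**Step 2: who has stopped work by 2 years.**
- Control: 1 - exp(-0.1277 × 2) = 0.225, and 0.225 × 263 = 59.
- Intervention: 1 - exp(-0.0830 × 2) = 0.153, and 0.153 × 263 = 40.
- Together about 99 of 526 (19%).
- Still working: about 204 controls and 223 intervention participants, before any loss to follow-up.

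The counts are approximate. Some people may be back at work by year 2, and some on short absences may also lack a score.

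**Step 3: how far selection moves the comparison.** Assumptions, none of them in the article: WIS is standard normal with the same distribution in both arms (no true effect, higher is worse). The cessation hazard is proportional to exp(bz), where z is the WIS score in SD units and exp(b) is the hazard ratio per SD. The control proportion still working at 2 years is fixed at 0.775, and the intervention multiplies the hazard by 0.65. The mean WIS among those still working, intervention minus control, is then:

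| Assumed cessation hazard ratio per SD of WIS | Shift against the program (SD) |
|---|---|
| 1.2 | 0.016 |
| 1.3 | 0.023 |
| 1.5 | 0.034 |
| 2 | 0.053 |
| 2.5 | 0.062 |
| 3 | 0.066 |

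A different model gives a similar range. With a normal latent tendency to stop work that correlates 0.3, 0.5 or 0.7 with WIS, the shift is 0.032, 0.054 or 0.075 SD.

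**Step 4: compare with the precision of the analysis.** With 204 and 223 people still working, the standard error of the difference is √(1/204 + 1/223) = 0.097 SD. Every shift above is smaller than one standard error.

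**The case against.** Presenteeism is by definition an at-work quantity, and a comparison among people who are working is a legitimate question. Work cessation is not ignored either. It is the second primary outcome, and its interim analysis falls at the same 2-year point, so readers would see it near the WIS result. The shift is below one standard error and runs against the program, so it cannot produce a false claim of benefit. All-cause cessation includes early retirement and personal reasons, which may weaken its link with WIS and favours the lower end of the range. All of this stands, and it limits the seriousness of the point. It does not remove the conflict, because a while-working comparison is not an analysis of everyone randomized.

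A reader might go further and infer that non-responders are also excluded, because the ANOVA uses only the 2-year value and imputation is named only for the economic evaluation. The article does not support that. No sentence limits the WIS analysis to responders, the ITT sentence states the opposite intent, and handling of drop-out may sit in the analysis plan, which is not shown. Nor can one say that this outcome could never be analysed by ITT, since a stated rule for people who stop work would resolve the conflict.

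Making worst-rank scoring the primary analysis is also open to challenge. It would count work cessation in both primary outcomes and would no longer isolate at-work productivity.

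**Conclusion.** The point holds as an inconsistency in a primary analysis. The article promises that every randomized patient is analysed, then names an analysis of a scale that has no value in people without work, and gives no rule to connect the two. On its own rates this affects about 22.5% of controls and 15.3% of intervention participants.

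The resulting bias is modest: about 0.02 to 0.07 SD over assumed hazard ratios of 1.2 to 3 per SD. Its direction rests on two conditions, that the program reduces cessation and that those who stop have worse WIS. The cost is lost power and a mislabelled result. It might be tempting to say that a true benefit would be hidden. That would need a target WIS difference to set the bias against, and the article gives none.

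**What to change.** 1. State the WIS estimand explicitly as a comparison while working, and do not describe it as ITT of all randomized patients.
2. Report the proportion working at 2 years, by arm, beside the WIS result.
3. Replace or support the single-timepoint ANOVA with a repeated-measures model on the six-monthly WIS scores, adjusted for baseline WIS as a planned covariate. People who later stop work then contribute the scores they gave. State how the model treats visits after cessation, because a standard mixed model implicitly extrapolates scores beyond that point.
4. Add a sensitivity analysis of everyone with known work status at 2 years, with work cessation ranked as the worst outcome.

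The cost is revised wording and modest extra programming, using data that the protocol already collects. The worst-rank analysis overlaps with the second primary outcome, so it should remain a sensitivity analysis and be read beside the proportion working.
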